##### 4.2.1.5 Olfactory capabilities

The European Test of Olfactory Capabilities (ETOC) will be used to assess the ability to identify and detect odorants. This test involves the presentation of 16 odorants at supraliminal concentrations. In each trial, 4 tubes are presented to the participants, only one of which contains the odorant. The aim of the task is to identify the tube containing the odorant, followed by identifying the specific odorant from a set of 4 propositions. Both tests are scored out of 16.

##### 4.2.1.6 Olfactory anhedonia

In addition, an olfactory hedonic judgment test will be assessed. It consists of the presentation of 20 odorants (with different hedonic value, from pleasant to unpleasant), 15 of which are monomolecular at a concentration of 20 Pa: isoamyl acetate, 2-phenylethanol, benzaldehyde, L-carvone, linalool, trans-anethol, benzyl-acetate, eucalyptol, cis-3-hexanol, citronellol, D-limonene, eugenol, n-caproic acid, trimethylamine, butyric acid, thioglycolic acid, and 5 are blended odorants: lemon/sweet orange/rosemary/bergamot/bitter orange/tree leaf/lavender/clary sage, linalool/d-limonene/linalyl acetate/beta-caryophyllene/beta-pinene/citral/geraniol/alphapinene/ eucalyptol/l-beta-bisabolene/menthone/geranyl acetate/2,6-dimethyl-5-heptenal/terpinolene, sweet orange/lavender/rosemary/bergamot/basil, vanilla extract/orange/ylang-ylang, and ylang-ylang/palmarosa/sweet orange/isoeugenol.

Participants will be allowed to freely smell each odorant presented in a randomized order. Then, participants will be asked to rate each odorant in terms of liking (“Is the smell pleasant?”), wanting (“Do you want to smell it again?”), intensity (“Is the smell intense?”), familiarity (“Is the smell familiar?”) (Chalençon et al., 2022). Each odorant will be rated on an analog scale ranging from 1 to 9 (1 for “Not at all,” 5 for “Neutral,” and 9 for “Extremely”).

#### 4.2.2 Behavioral assessment

##### 4.2.2.1 Eye tracking free-viewing task

The Free Viewing Task (FVT) will assess attentional emotional bias before the treatment and after 1, 5, and 50 rTMS sessions, as it correlates with depression severity (Imbert et al., 2024). This makes it a relevant outcome to evaluate before and after treatment, providing objective measures of improvement. In the task, pairs of faces: one emotional (happy or sad) and one neutral, are presented randomly for 3,500 ms to the right and left of a fixation cross. The inter-stimulus interval is randomized among 1,250, 1,500, or 1,750 ms, and the next pair appears only when the participant fixates on the cross. A total of 32 pairs (16 happy- neutral, 16 sad-neutral pairs), with 16 different identities (8 males, 8 females), will be presented. The faces are extracted from the FACES database (Ebner et al., 2010).

Throughout the task, gaze position and eye movements are recorded using an eye-tracking system (SMI SensoMotoric Instruments with BeGaze 3.6.52, Teltow, Germany).

We will assess early and sustained attention allocation using eye-movement recordings. Sustained attention will be measured by dwell time (DT), the total time spent fixating on faces. The emotional bias score will be the difference between DTs for emotional and neutral faces. Early attention will be measured by the orientation of the first saccade, the first face the participant looks at. The laterality quotient will be the difference between the number of first saccades to emotional vs. neutral faces, divided by the total trials. Positive values indicate a bias toward emotional faces; negative values indicate a bias toward neutral faces.

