#### 1.2.2 Secondary objectives

##### 1.2.2.1 Clinical outcomes

We will assess the acute and long-term effects of the treatment on several clinical features of MDD: remission (MADRS_10_ < 10) and response (reduction of at least 50% in MADRS_10_ score), severity of self-rated depression (BDI_13_), physical and social anhedonia and apathy immediately after the treatment, after 1-month and 3-month follow-up.

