##### 1.2.2.2 Behavioral outcome

We will investigate the effect of the treatment on cognitive biases using a free viewing task (see 4.2.2.1 Eye tracking free-viewing task), at baseline, after 1, 5, and the 50 sessions of rTMS.

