#### 2.4.2 Other clinical and behavioral outcomes

Several clinical and behavioral features will be assessed using:

- the 10-item MADRS total scores to assess depression severity.- the number of responders, defined as those who show a reduction of at least 50% in their MADRS score.- the 13-item Beck Depression Inventory (BDI) (Gould, 1982), to assess self-rated depression.- the 11-item Young Mania Rating Scale (YMRS) (Young et al., 1978), to assess manic states.- the Childhood Trauma Questionnaire (CTQ) (Bernstein et al., 2003) to study early life adversity.- the Chapman Social Anhedonia Scale and the Chapman Physical Anhedonia Scale (Chapman et al., 1976) to investigate respectively physical and social anhedonia.- the Snaith-Hamilton Pleasure Scale (SHAPS) (Snaith et al., 1995) to assess global anhedonia.- the Apathy Evaluation Scale (AES) (Marin et al., 1991) to assess apathy.- the Free-Viewing task (FVT) to assess cognitive biases, more precisely, early and sustained emotional attentional biases.

These outcomes will be assessed before and after the 50 iTBS sessions. The same outcomes will also be assessed at 1 and 3 months after treatment and compared between the two groups. In addition, the relationship between early life adversity and depression severity will be examined, as well as its association with the evolution of depressive symptoms and especially anhedonia.

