**Assessments:**							
MADRS	**X**	**X**		**X**	**X**	**X**	
BDI		**X**		**X**	**X**	**X**	**X**
CTQ		**X**					**X**
Chapman scales		**X**		**X**	**X**	**X**	
SHAPS		**X**		**X**	**X**	**X**	**X**
AES		**X**		**X**			**X**
ETOC/hedonic perception		**X**					**X**
FVT		**X**		**X**			
MRI		**X**		**X**			
Dual-site TMS		**X**		**X**			**X**

iTBS, intermittent Theta Burst Stimulation; MDD, Major Depressive Disorder; MADRS, Montgomery and Asberg Depressive Rating Scale; BDI, Beck Depression Inventory; CTQ, Childhood Trauma Questionnaire; SHAPS, Snaith-Hamilton Pleasure Scale; AES, Apathy Evaluation Scale; ETOC, European Test of Olfactory Capabilities; FVT, Free-Viewing Task; MRI, Magnetic Resonance Imagery; TMS, Transcranial Magnetic Stimulation.

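### Table 1 omits assessments that two secondary objectives need: the free-viewing task after sessions 1 and 5, and apathy at 1 and 3 months

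*Protocol article*

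**What the plan says.** **Free-viewing task.** The behavioural objective (1.2.2.2) sets the task "at baseline, after 1, 5, and the 50 sessions of rTMS". The description of the task (4.2.2.1) agrees: it "will assess attentional emotional bias before the treatment and after 1, 5, and 50 rTMS sessions".

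**Apathy.** The clinical objective (1.2.2.1) covers acute and long-term effects and names "physical and social anhedonia and apathy immediately after the treatment, after 1-month and 3-month follow-up". Section 2.4.2 lists the AES among its outcomes and says of the whole list: "These outcomes will be assessed before and after the 50 iTBS sessions". It then adds: "The same outcomes will also be assessed at 1 and 3 months after treatment and compared between the two groups". The same list contains "the Free-Viewing task (FVT) to assess cognitive biases, more precisely, early and sustained emotional attentional biases".

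**Table 1 (section 2.5).** The patient columns are weeks -1, 0, 1, 2, 6 and 14. The FVT row is marked at weeks 0 and 2. The AES row is marked at weeks 0 and 2 for patients, and once more at the healthy-volunteer visit. Neither row has a mark at week 1, 6 or 14.

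**The concern.** The schedule table is what site staff are most likely to work from. If they do, two things that the objectives ask for are never collected.

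- **Early attentional bias.** The runs after sessions 1 and 5 separate an early shift in bias from one that appears only after the full course. A baseline run and an end-of-treatment run cannot show that.
- **Durability of apathy change.** The AES asks about the month before the assessment (4.2.1.4), and the course lasts two weeks. A form completed at the end of treatment therefore looks back partly over time before treatment began. The 1-month form is the first whose reference month lies after treatment, so its absence costs more than one extra point on a curve.

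A missed run or form cannot be reconstructed afterwards. The choice of schedule also decides what the GROUP × TIME test of section 4.4.1.3 tests for the FVT: a simple pre-post contrast or a course over four occasions.

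**Working it through.** The protocol gives no figure to reproduce here. The check sets the text against the table, row by row.

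| Instrument | Time points in the text | Marks for patients in Table 1 | In the text but not in the table |
|---|---|---|---|
| FVT | Baseline; after sessions 1, 5 and 50 (1.2.2.2, 4.2.2.1) | Weeks 0, 2 | After session 1; after session 5 |
| AES | Before; after; 1 month; 3 months (1.2.2.1, 2.4.2) | Weeks 0, 2 | 1 month; 3 months |
| MADRS | After; 1 and 3 months (1.2.2.1) | Weeks -1, 0, 2, 6, 14 | None |
| BDI | After; 1 and 3 months (1.2.2.1) | Weeks 0, 2, 6, 14 | None |
| Chapman scales | After; 1 and 3 months (1.2.2.1) | Weeks 0, 2, 6, 14 | None |
| SHAPS | Before; after; 1 and 3 months (2.4.2) | Weeks 0, 2, 6, 14 | None |

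**Could the table have been damaged in extraction?** This is unlikely. The MADRS, BDI, Chapman and SHAPS rows carry their marks at weeks 6 and 14. In the AES row the healthy-volunteer mark still falls in the last column, after two empty cells, so the columns are aligned. The blanks belong to these rows.

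**Could the marks at weeks 0 and 2 already cover sessions 1 and 5?** No. Section 2.3 gives 5 sessions per working day, so sessions 1 to 5 all fall on treatment day 1. Table 1 places the interventions in the post-allocation columns, starting at week 1. The week 0 mark precedes treatment and the week 2 mark follows it.

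**Size at full attendance.**

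- FVT runs after sessions 1 and 5: 80 × 2 = 160.
- AES forms at weeks 6 and 14: 80 × 2 = 160.

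With the 74 patients that section 2.6.1 requires before its allowance for attrition, each count is 74 × 2 = 148. These counts describe collection effort. They are not measures of bias or of lost power.

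**Effect on the FVT model.** With two groups and k occasions, the GROUP × TIME interaction has (2 − 1)(k − 1) = k − 1 numerator degrees of freedom. Table 1 gives k = 2, hence 1. Sections 1.2.2.2 and 4.2.2.1 give k = 4, hence 3. The first asks whether the pre-post change differs between groups, and the second whether the course over treatment differs.

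**The case against.** A reader might infer more than the document supports. Four stronger readings should be set aside.

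- **That these questions will have no data.** This follows only if Table 1 overrides the text. Section 2.5 offers the table as an overview, and it is incomplete elsewhere. The YMRS, listed in 2.4.2, has no row. Olfactory hedonic testing, promised after treatment and at follow-up in 1.2.2.4 and 2.4.4, is marked for patients only at week 0. A blank cell is therefore weak evidence that a measure will be left out. What stands is an unreconciled contradiction with a risk attached.
- **That the FVT has three rival schedules, or six time points in all.** This rests on the sentence in 2.4.2 that sends its whole list to 1 and 3 months. The list also contains the CTQ, a childhood-trauma questionnaire that Table 1 schedules once for patients, so the sentence was evidently not written instrument by instrument. No objective asks for a long-term FVT. The two FVT-specific passages agree with each other, and the real conflict is between them and the table.
- **That long-term effects in general go unmeasured.** Of the features named in 1.2.2.1, only apathy lacks marks at weeks 6 and 14.
- **That section 4.4.1.3 is defective because it does not list the levels of TIME.** A protocol commonly leaves that to the analysis plan, which is not shown.

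It might also be said that an article may condense such detail. That would excuse an omission. Here two printed statements disagree, and section 7.3 presents the article as the full protocol, so it points to no other document that would settle the matter.

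**Conclusion.** The point holds as a contradiction between Table 1 and two stated secondary objectives. Two FVT occasions (after sessions 1 and 5) and two AES occasions (1 and 3 months) stand in the text and are missing from the schedule. At full attendance that is 160 assessments for each instrument.

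The loss is conditional: it occurs if staff follow the table. The document does not show whether the table or the text is in error.

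The primary outcome, MADRS remission at the end of the 50 sessions, is scheduled and unaffected, and the sample size and the interim rule are not touched. This should be corrected because the correction is cheap and the data cannot be recovered later, but it does not threaten the main conclusion of the trial.

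**What to change.** Make the table and the text agree, in one of two ways.

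1. **Keep the objectives.** Mark the FVT in Table 1 after sessions 1 and 5, both on treatment day 1, and mark the AES at weeks 6 and 14 beside the BDI and SHAPS.
2. **Keep the table.** Withdraw the runs after sessions 1 and 5 from 1.2.2.2 and 4.2.2.1, and the 1- and 3-month apathy assessments from 1.2.2.1 and 2.4.2.

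Under either choice, limit the 1- and 3-month sentence in 2.4.2 to the instruments scheduled at those visits. That excludes the FVT unless follow-up runs are intended, in which case Table 1 should show them. The FVT occasions that enter TIME can then be listed in the analysis plan.

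The second choice costs only an edit, but it gives up two stated questions. The first adds an 18-item self-report form at two visits that patients already attend, and two 32-pair eye-tracking runs on a day when they are already on site. The downside is a little extra patient time.

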#### 4.2.3 Neurobiological investigations

##### 4.2.3.1 Functional connectivity with magnetic resonance imaging

The MRI sequences will include, for anatomical measurements, a sagittal 3D T1-weighted sequence that will be acquired in about 8 min. The standardized parameters will ensure good contrast and whole-brain coverage with 0.8-mm isotropic resolution. A fieldmap will be acquired to correct for geometrical distortions induced by the EPI sequence. For functional measurements through changes in BOLD T2^*^-weighted signals, a 2D axial gradient echo EPI sequence will be acquired in 12 min. The standardized parameters will ensure maximum brain coverage with 2.7 mm isotropic voxels, a repetition time equal to 1.7 s, and 420 repetitions for ensuring statistical significance could be reached during the following analyses. Participants will be instructed to keep their eyes closed during the functional acquisition.

All MRI acquisitions will be performed at the CERMEP Multimodal Imaging Platform (Lyon, France) using a 3-Tesla MR Siemens Prisma scanner with a 64-channel head coil.

Imaging data will be pre-processed and analyzed according to the latest standard procedures available at the time of analysis.

##### 4.2.3.2 Effective connectivity with Dual-site transcranial magnetic stimulation

The MagStim 200^2^ BiStim^2^ dual-site TMS (MagStim, United Kingdom), connected to two 40 mm figure-of-eight coils, will be used to probe effective connectivity from the left DLPFC to the left M1 both at rest and during odor perception (pleasant and unpleasant odorants) sent using an olfactometer (Wang et al., 2020; Neige et al., 2023). When the olfactometer (Sezille et al., 2013) detects the exhalation phase, it initiates an airflow through tubes containing the odorant for 6 seconds. This odorant-charged airflow is delivered to the participant via nasal canula. At 600 ms following the onset of the inhalation phase, which represents the maximum conscious representation of the odorant (Kato et al., 2022), the olfactometer trigs the TMS to deliver a pulse to the DLPFC. After a brief delay, a trigger is sent to the TMS connected to M1 to administer a pulse.

This measure will be realized before and after the 50 sessions of iTBS. Motor-evoked potentials (MEP) will be recorded using surface electromyography (BIOPAC, United States of America) from the right FDI. The conditioned MEP peak-to-peak amplitude evoked by dual-site TMS will be compared to the MEP amplitude evoked by TMS applied over M1 alone (see Neige et al., 2023) for the detailed protocol of this experiment.

#### 4.2.4 Plans to promote participant retention and complete follow-up

##### 4.2.4.1 Patients with MDD

To encourage adherence to the protocol and to compensate for the time spent in the hospital, participants will receive 150 euros to cover travel, food expenses, and MRI sessions. The given amount will depend on the number of visits attended.

To minimize loss to follow-up, each participant will receive an individualized schedule of all visits at the beginning of their inclusion. Additionally, the research assistant will contact participants a few days before their scheduled appointments as a reminder.

##### 4.2.4.2 Healthy volunteers

A single visit is planned for healthy volunteers, thus limiting the loss rate. They will receive 50 euros for their participation in the study, with a further 10 euros to cover travel costs.

### 4.3 Data management

Sociodemographic and clinical data will be collected using a Case Report Form (CRF) that is stored in a secure cabinet. All the data will be reported in a secure tabular file stored on a secure server. Two-person double checks will be performed to verify the accuracy of the reported data.

MRI data will be accessible via the secure server of the neuroimaging platform and will be stored on the hospital's server.

### 4.4 Statistical methods

#### 4.4.1 Statistical methods for analyzing primary and secondary outcomes

Statistical analysis will be performed using R studio (Boston, USA, with the latest version at the time of the analysis) by an experimenter blinded to treatment allocation. The alpha threshold will be fixed at 0.05. Parametric tests will be performed only when the assumptions for their application are met, otherwise, non-parametric tests will be performed.

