### 2.6 Sample size

#### 2.6.1 Patients with MDD

The sample size was estimated using EasyMed online software (https://easymedstat.fr), with an a priori power analysis based on a comparison of two binomial proportions (approximation of arscin).

We expect an approximately twofold increase in the remission rate for the iTBS combined with olfactory training group, compared to the iTBS alone group. This expectation is based on results from similar protocols using dual activation of the same neural network, such as the combination of high-frequency rTMS and visual smoking cues in individuals with tobacco use disorder, which reported 1.8-fold higher remission rate in the combination group than in the rTMS group alone (Dinur-Klein et al., 2014), and deep TMS with exposure in patients with post-traumatic stress disorder (Isserles et al., 2013), which reported a 3.5-fold higher response rate in the combination group than in the rTMS alone group.

Based on previous studies investigating the clinical efficacy of rTMS in treatment-resistant depression in both RCTs (Vida et al., 2023) and naturalistic settings (Bouaziz et al., 2023), we predict an approximate remission rate of 30% for the iTBS alone group. Thus, the expected remission rate for the iTBS combined with olfactory training group is estimated to be 60%. With a chi-squared test, an α risk of 5%, and a ß-power of 80%, a total of 74 MDD patients (37 per group) are required to be included.

As all patients enrolled in this trial will receive active treatment, we anticipate a low attrition rate (7%) and therefore plan to recruit a total of 80 patients with MDD (40 per group).

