#### 5.1.2 Interim analysis

Given the pilot nature of this study, we plan to conduct an interim efficacy analysis when 40 patients (50% of the total sample) have been included. This analysis will allow for the earliest detection of the benefit of adding hedonic olfactory stimulation, thus accelerating its availability to patients. During this interim analysis, the same primary and secondary analyses will be performed as at the end of the study. To reduce a type I error (related to α-risk inflation), the spending function of α risk proposed by O'Brien and Fleming (1979) will be used, with a stopping boundary (expressed in *P*-value) set at 0.005 for the interim analysis and 0.048 for the final analysis (Schulz and Grimes, 2005). The study will be stopped if a statistically significant difference in remission rates between the two groups is observed immediately after treatment. No futility analysis is planned.

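### All secondary analyses are repeated at the interim with 0.05 as their only stated level, and section 4.4.1 does not say that the final primary test uses 0.048

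*Protocol article*

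**What the plan says.** Section 4.4.1, headed as covering both primary and secondary outcomes, gives one level: "The alpha threshold will be fixed at 0.05". It does not call this the overall level and does not mention the interim analysis.

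Section 5.1.2 plans one interim efficacy analysis "when 40 patients (50% of the total sample) have been included". It adopts an O'Brien-Fleming approach to limit alpha inflation, with boundaries "set at 0.005 for the interim analysis and 0.048 for the final analysis". At the interim, "the same primary and secondary analyses will be performed as at the end of the study". The stopping rule uses the primary outcome only: "The study will be stopped if a statistically significant difference in remission rates between the two groups is observed immediately after treatment".

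Section 2.4.1 reads remission at the end of the 50 sessions. Table 1 places inclusion at week -1, the post-treatment assessment at week 2 and the follow-up visits at weeks 6 and 14. Section 4.4.2 limits the analysis to patients with at least one post-treatment evaluation.

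**The concern.** Three things need settling before any data are seen.

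- **Final primary threshold.** A reader of section 4.4.1 alone would test remission at 0.05. A reader of section 5.1.2 would use 0.048. The plan should state the final threshold once.
- **Secondary outcomes at the interim.** The boundaries are introduced to limit alpha inflation, and the stopping rule is tied to remission. The secondary outcomes are nevertheless all analysed at the interim too, and the only level given for them is the unqualified 0.05. Two tests at 0.05 on accumulating data, with a positive claim possible at either, carry more than a 5% error. The stopping rule makes no use of these comparisons.
- **Trigger.** The look is tied to 40 inclusions, while remission is read about three weeks after inclusion and follow-up ends at week 14. At the 40th inclusion some of those patients have no primary outcome, and more lack follow-up data. An analysis of the 1- and 3-month outcomes as at the end of the study could not then be complete.

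**Working it through.** **Inputs.** General level 0.05 (section 4.4.1). Boundaries 0.005 and 0.048, with the interim at 40 of 80 patients, so information fraction t = 0.5 (section 5.1.2). Sidedness is not stated; I take the tests as two-sided, in line with the chi-squared test of section 2.6.1.

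**Formula.** The standardised statistics at the two looks, Z1 and Z2, are bivariate normal under the null with correlation √t. With critical values c1 and c2,

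overall error = 1 − P(|Z1| < c1 and |Z2| < c2).

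Two-sided critical values: 0.005 → 2.807; 0.048 → 1.977; 0.05 → 1.960.

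**Step 1: the plan's own boundaries.** The classical two-look O'Brien-Fleming design has c1 = c2·√2. Solving for an overall 0.05 at √0.5 = 0.707 gives c2 = 1.977 and c1 = 2.797, that is p = 0.0480 and 0.0052. The Lan-DeMets spending version gives 0.0478 and 0.0056. The stated pair 0.005/0.048 is therefore reproduced.

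**Step 2: overall error at t = 0.5.**

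| Interim level | Final level | Overall two-sided error |
|---|---|---|
| 0.005 | 0.048 | 0.0499 |
| 0.005 | 0.05 | 0.0519 |
| 0.05 | 0.05 | 0.0831 |

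The first row is the primary outcome as section 5.1.2 sets it. The second is the primary outcome if 0.05 were used at the end; its excess over 0.05 is 0.0519 − 0.05 = 0.0019. The third is one secondary outcome tested at 0.05 at both looks with a claim allowed at either.

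**Step 3: does the range 0.048 to 0.05 matter in practice?** I enumerated all 2×2 remission tables with equal arms of 37 and of 40. With the uncorrected chi-squared test, no table has a p-value above 0.048 and up to 0.05. With the continuity correction or Fisher's exact test, such tables have a probability of at most 0.7% under any common remission rate, and at most 0.25% at the planned 30% versus 60%. Unequal arms were not enumerated.

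**Step 4: the trigger.** Suppose that 32 of the first 40 patients have a post-treatment MADRS when the look is taken. This is an assumption, as the plan gives no accrual rate. Then t = 32/80 = 0.40, and 0.005/0.048 gives an overall error of 0.0505. The effect on the primary outcome is small. The lag from inclusion to the primary outcome is 2 − (−1) = 3 weeks in Table 1. To the last follow-up it is 14 − (−1) = 15 weeks, so secondary data at the interim are much less complete than remission data.

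**The case against.** The strongest objection is that nothing is contradictory. Section 4.4.1 never calls 0.05 the level of the final primary test, section 2.6.1 gives 5% as the design level, and 0.048 is what an overall 0.05 implies after 0.005 at half information. This stands. A reader might infer that the two sections cannot both hold, or that error control is lost. The documents do not support that: the primary outcome has its own boundary pair, the worst reading adds 0.0019, and few or no attainable tables fall between the two thresholds.

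It can also be said that the 8.3% rests on an assumption. That is correct. No section says that secondary outcomes are tested at 0.05 at the interim or that a claim may be made at either look. Interim secondary tests cannot stop the trial, so they do not inflate the primary error. No family-wise control is claimed for secondary outcomes, and multiplicity across them is commonly left to an analysis plan, so it is not raised here. What remains is a stated procedure, not an omission: section 5.1.2 prescribes the repeated analyses, and 0.05 is the only level given for them.

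On the trigger, a remission test immediately after treatment arguably implies waiting for that assessment, and section 4.4.2 excludes patients without one. This makes the point small for the primary outcome. It does not help the week-6 and week-14 analyses.

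Finally, a reader might infer that the team recruiting and rating patients would see the interim arm differences. The protocol does not say who receives the results. Sections 3.4, 4.4.1 and 6.6 keep raters, analysts and patients blinded. Unblinding by the interim is therefore not shown. A limit on what is released is a precaution only.

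**Conclusion.** The point holds as a minor to moderate one. For the primary outcome the plan is sound (overall error 0.0499) but should state the final threshold once, as 0.048; using 0.05 would give 0.0519. The more material part is the repetition of all secondary analyses at an interim whose stopping rule does not use them. It gives about 8.3% error per secondary outcome if each is tested at 0.05 at both looks and a claim is allowed at either, and it would rest on incomplete follow-up data. The figures assume two-sided tests, approximate normality and half the information at the interim. An inclusion-based trigger that yields 40% information would move the primary error only to about 0.0505.

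**What to change.** **Section 4.4.1.** State that 0.05 is the overall two-sided level; that the primary remission test uses 0.005 at the interim and 0.048 at the final analysis; and that secondary outcomes are tested once, at the final analysis, or at the interim only if the trial stops there.

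**Section 5.1.2.** Restrict the interim to post-treatment (week-2) remission. Perform it when the first 40 randomised patients have passed their week-2 assessment, in place of the count of inclusions. Release only the decision to stop or continue to the trial team.

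**Cost.** The statement of levels is wording only. Dropping the interim secondary analyses removes something that the plan now includes, so it is a small design change: there is no early look at secondary outcomes, and the interim comes a few weeks later. The interim workload falls, and the primary boundaries do not change.
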